### Sample Size and Power Calculations

The minimum sample for each group was identified as 64 participants to detect a power of 0.80 and an α of 0.05. These calculations were performed using the G^*^Power 3.1 software for comparison between two intervention groups with respect to the mean differences of the scores at each time point of assessment relative to baseline. Therefore, 152 individuals should be randomized to receive one of the interventions (76 in the intervention group, 76 in the control group) assuming a maximum loss of 15%.

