### Statistical Analysis

All analyses will be conducted using intention-to-treat and per-protocol analyses following the CONSORT recommendations for reporting the results (44).

Categorical variables will be described by absolute and relative frequencies. Numerical variables will be checked for their distributions through histograms and boxplots. If considered as having normal distribution, they will be described by mean and standard deviation. Otherwise, they will be described by medians and quartiles.

The primary outcome of this study is the quality of life measured by the WHOQOL-BREF and WHOQOL-OLD, and the secondary outcomes are cognitive function measured by the MoCA, level of consciousness at present measured by the MAAS, self-compassion measured by the SCS, Psychological Health measure by DASS-21, sleep quality measured by PSQI, and religiosity assessed by the Duke University Religion Index. Sociodemographic questions (sex, age, schooling), treatment group, and time will be the independent variables.

To verify the homogeneity between the study groups regarding sociodemographic measures at the initial time of the study, the groups will be compared by means of hypothesis tests of the type: χ^2^ and/or Fisher exact for categorical variables and multivariate analysis of variance (MANOVA) and/or Kruskal–Wallis for numerical or ordinal variables. A descriptive analysis of the sociodemographic categories regarding the sex, age, and schooling of both groups will be carried out.

Measures of preintervention (T0), post-intervention (T1), and follow-up (T2) outcomes may be compared by means of MANOVA for repeated measures. If necessary, Student *t*-tests will be conducted for paired or Wilcoxon data by applying corrections by the Holm or Bonferroni method. A Pearson correlation coefficient analysis will also be performed between the means of the primary outcomes and those of the secondary outcomes to examine the degree of changes in the outcome measures over time.

The difference between the measures T0 to T1, T1 to T2, and T0 to T2 can be compared between the intervention groups in MANOVA of repeated measures by means of Mann-Whitney tests. If necessary, these models will also be adjusted to assess the effects of time and intervention group, controlling for possible moderating variables.

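### Baseline significance tests cannot verify that randomised arms are homogeneous, and the plan leaves open whether the quality-of-life contrast is adjusted

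*Protocol article*

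**What the plan says.** All the analysis statements are in the Statistical Analysis section of the protocol article.

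- **Purpose of the baseline comparison:** "To verify the homogeneity between the study groups regarding sociodemographic measures at the initial time of the study, the groups will be compared". The tools are chi-square and/or "Fisher exact for categorical variables and multivariate analysis of variance (MANOVA) and/or Kruskal–Wallis for numerical or ordinal variables". No size of imbalance is named as acceptable or unacceptable.
- **Description:** "A descriptive analysis of the sociodemographic categories regarding the sex, age, and schooling of both groups will be carried out". This comes in addition to the tests.
- **Covariates, without condition:** "Sociodemographic questions (sex, age, schooling), treatment group, and time will be the independent variables".
- **Adjustment, with a condition:** "If necessary, these models will also be adjusted to assess the effects of time and intervention group, controlling for possible moderating variables". Neither the trigger nor the variables are given.
- **Between-arm comparison:** "The difference between the measures T0 to T1, T1 to T2, and T0 to T2 can be compared between the intervention groups". The sentence goes on to name both a repeated-measures MANOVA and Mann-Whitney tests.

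The Sample Size and Power Calculations section gives the numbers per arm: "The minimum sample for each group was identified as 64 participants to detect a power of 0.80 and an α of 0.05" and, allowing for 15% loss, "152 individuals should be randomized to receive one of the interventions (76 in the intervention group, 76 in the control group".

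**The concern.** There are two linked problems.

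First, a difference test does not fit the stated purpose. With random 1:1 allocation the null hypothesis of no systematic difference holds by design. A significant result is then a chance event, and a non-significant one is not evidence of similarity. The p-value also takes no account of whether a covariate predicts quality of life, which is what decides whether an imbalance matters.

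Second, the text on adjustment points two ways. One sentence puts sex, age and schooling among the independent variables outright. Another makes adjustment depend on need and refers to unnamed moderators, which suggests that the default models are unadjusted. The Mann-Whitney test on changes cannot include covariates at all. An analyst could follow any of these routes and claim to have followed the plan.

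At stake are the precision of the primary contrast, its conditional bias if a prognostic covariate happens to be unbalanced, and the freedom to choose between adjusted and unadjusted results once both are known.

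**Working it through.** **Inputs from the document.** 76 randomised and 64 analysable per arm, alpha 0.05, power 0.80, 15% loss, 1:1 allocation.

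**Assumptions, because the document gives no figure.** Two-sided testing, an effect of 0.5 SD, independent covariates and their correlations with the outcome. Keeping couples together is ignored.

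**1. The plan's own figure.** A two-sided two-sample t-test with d = 0.5, alpha 0.05 and power 0.80 needs 63.8, so 64 per arm. Then 64 / 0.85 = 75.3, so 76 per arm. The stated numbers reproduce if d = 0.5, which is inferred.

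**2. What a baseline test can flag.** All randomised participants enter the baseline comparison, so n = 76. A t-type test on one numerical covariate is significant when the observed standardised difference exceeds

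t(0.975; 150 df) × √(2/76) = 1.976 × 0.1622 = 0.32 SD.

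Below that it is never significant; above it, always. For a two-variable MANOVA with the imbalance in one variable only, the bar is higher: an observed 0.4 SD gives about p = 0.052.

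**3. How often imbalance arises by chance.** The observed difference has standard error 0.1622 SD (normal approximation).

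| Event | Probability |
|---|---|
| One covariate differs by more than 0.2 SD | 22% |
| One covariate differs by more than 0.3 SD | 6% |
| At least one of three covariates differs by more than 0.2 SD: 1 − (1 − 0.218)³ | 52% |
| At least one of three tests significant: 1 − 0.95³ | 14% |

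Of the imbalances above 0.2 SD on one covariate, about (0.218 − 0.05) / 0.218 = 77% are not significant.

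**4. Size of the conditional shift.** If left unadjusted, the shift in the arm difference is the correlation times the imbalance. At 0.3 SD, just under the flagging limit:

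| Assumed correlation with outcome | Shift (SD) | Share of a 0.5-SD effect |
|---|---|---|
| 0.1 | 0.03 | 6% |
| 0.2 | 0.06 | 12% |
| 0.3 | 0.09 | 18% |
| 0.5 | 0.15 | 30% |

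**5. Precision from always adjusting.** With three independent covariates each correlated r with the analysed outcome, R² = 3r² and the effective standardised effect is 0.5 / √(1 − R²). Power at 64 per arm:

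| r | R² | Effective d | Power |
|---|---|---|---|
| unadjusted | 0 | 0.500 | 80% |
| 0.1 | 0.03 | 0.508 | 81% |
| 0.2 | 0.12 | 0.533 | 85% |
| 0.3 | 0.27 | 0.585 | 91% |

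**6. Baseline score of the outcome.** Against an analysis of change, adjusting for the baseline score multiplies the variance by (1 + ρ)/2, where ρ is the baseline to follow-up correlation. If the effect on change is 0.5 SD, power at 64 per arm goes from 80% to 90%, 86% or 84% for ρ = 0.5, 0.7 or 0.8.

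**7. Type I error.** Simulation at 64 per arm, with covariate correlations of 0.2 or 0.3, gave rejection rates of 4.4% to 5.6% under no effect, whether covariates were never adjusted for, adjusted for only when unbalanced, or always adjusted for.

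**The case against.** The strongest reply is that this is loose wording in a condensed article. The plan names sex, age and schooling as independent variables, already promises a descriptive comparison, and works with changes from T0 or repeated measures, which partly account for the baseline level of the outcome. A covariate list could properly sit in an analysis plan that is not shown. The gain is modest unless all three demographics are clearly prognostic, and they may correlate less with change than with level.

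Much of that stands, and it limits the severity. It does not remove the point, which rests on what the article states: tests given a purpose they cannot serve, and sentences on adjustment that do not agree.

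Three stronger readings are tempting and not supported.

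- *The tests would miss relevant imbalances at some fixed rate.* Type II error at 76 per arm can be computed (55%, 31% and 13.5% for a t-test at 0.3, 0.4 and 0.5 SD), but against true population differences, which randomisation rules out. Only the observed imbalance can confound. An observed 0.4 or 0.5 SD gives t-test p = 0.015 or 0.002 and is flagged.
- *A non-significant baseline test switches adjustment off.* No sentence says so. The condition on adjustment appears later, concerns moderators, and is not tied to the baseline tests.
- *Confounding goes uncorrected.* The sentence listing the covariates supports adjustment. It may or may not be done; the text does not settle which.

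**Conclusion.** The point holds as a minor to moderate defect. Baseline significance tests cannot verify the homogeneity of randomised arms, and the section leaves adjustment of the primary contrast open to a decision made after the data are seen.

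The size rests on assumed values. With d = 0.5, 64 per arm and three independent covariates, the power forgone is about 1, 5 or 11 percentage points at correlations of 0.1, 0.2 or 0.3. The largest figure needs the three demographics together to explain 27% of the outcome variance, so it is the optimistic end. An unadjusted 0.3-SD imbalance would shift the estimate by 0.03 to 0.15 SD for correlations of 0.1 to 0.5.

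Chance imbalance does not inflate the overall type I error. A choice between adjusted and unadjusted results after seeing both is a separate risk, and its size was not estimated here.

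**What to change.** In the Statistical Analysis section:

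1. Delete the baseline hypothesis tests (chi-square, Fisher, MANOVA, Kruskal-Wallis) and the stated aim of verifying homogeneity. Describe baseline by arm with means and SDs, medians and quartiles, or counts, and add standardised differences.
2. Replace the conditional adjustment sentence with a prespecified between-arm model for WHOQOL-BREF and WHOQOL-OLD that always includes the baseline score of that outcome, sex, age and schooling, whatever their observed balance.
3. Reconcile the Mann-Whitney comparison of changes with that model. If it is kept, label it as an unadjusted supporting analysis.

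The change needs no new data or participants, since these variables are already collected at recruitment. It costs a few degrees of freedom, and the first results table will carry no p-values.

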## Materials and Methods

The “MBHP-Elderly Study” is a randomized controlled trial addressing older people with 3 assessment points (baseline, post-intervention, and 1-year follow-up) nested in a cohort study (the EPIDOSO study) of older adults patients assisted in a PC facility of the “Center for Aging Research” [Centro de Estudos do Envelhecimento (CEE)] of the Universidade Federal de São Paulo—UNIFESP.

One hundred fifty-two participants will be recruited from the cohort and then randomized into the following two experimental groups: (I) MBHP intervention group (76 participants) in which the elderly will have a weekly meeting of an hour and 30 min for 8 weeks to perform the MBI (MBHP protocol) accompanied by extra four 1-h meetings through a maintenance group with all participants after the eighth week (each maintenance session took place fortnightly), totaling a 4-month (16-week) intervention; (II) cognitive stimulation control group (76 participants) of elderly who will take computer-based cognitive stimulation classes for 4 months, once-a-week 1.5-h meetings without maintenance phase, totaling 16 weeks. In both groups, the same assessment for data collection will be applied, and they will be applied in the baseline (T0), post-intervention (T1), and 1-year follow-up (T2). Both interventions will last 16 weeks. However, the reason why the MBHP intervention group will take 12 sessions and the cognitive stimulation control group 15 sessions is because one of the aims in the MBHP intervention is to work on the participants' autonomy in their personal mindfulness practice in daily life through home activities exercises, and we wanted to compare its outcomes with the 4-month weekly meetings of control intervention, which require face-to-face sessions. Study design and participant flow through the trial is shown in Figure 1.

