One potential limitation of the study is the lack of a second and passive control group composed of a waiting-list participant, besides the active control group. There is a growing discussion over the use of waiting-list control group in psychological and behavioral research (87). Some researchers will argue that to evaluate the effects of interventions it is better to have three groups: an intervention, an active control group of a treatment as usual, and a passive control group that does not receive any treatment. Due to ethical issues (both mindfulness and cognitive stimulation are expected to promote positive effects based on previous studies) and the well-known difficulties to recruit a large number of older persons to research protocols, we decided to opt for two groups with a statistically sound calculated sample.

Furthermore, the fact that when multiple constructs are being measured using common methods and surveys may lead to spurious effects due to the measurement instruments rather than to the constructs being measured is well-known. For instance, false correlations are likely to be produced among the items owing to response styles or social desirability.

Despite these limitations, the present study, which uses qualitative and quantitative approaches, may bring a better understanding of how MBIs may improve the quality of life in objective and subjective perspectives within a mixed-methods approach. Psychometrics parameters and qualitative assessment through focus group and the word free evocation technique may bring a range of meaningful data to find out how mindfulness training may work on older people and if the MBHP program is feasible and efficacious when applied for older population in PC.

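### The planned correlation of outcome means does not serve its stated purpose of examining change over time; individual change scores should be correlated, or the purpose dropped

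*Protocol article*

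**What the plan says.** In the protocol article, Statistical Analysis, the paragraph on repeated-measures comparisons ends with a supporting analysis: "A Pearson correlation coefficient analysis will also be performed between the means of the primary outcomes and those of the secondary outcomes". The same sentence gives its purpose: "to examine the degree of changes in the outcome measures over time". It does not say whether a mean is taken per person, per visit or per arm, and it does not mention change scores.

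The next paragraph does name change scores, but for another use: "The difference between the measures T0 to T1, T1 to T2, and T0 to T2 can be compared between the intervention groups". All the outcomes concerned are measured at T0, T1 and T2 (Table 2), so individual differences can be formed for each of them.

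The Discussion, in its limitations, warns that with common survey methods "false correlations are likely to be produced among the items owing to response styles or social desirability".

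**The concern.** The method and its purpose do not match. The question is about change; the quantity to be correlated is a level. People who generally rate their lives well may also generally report more self-compassion or better sleep. That stable difference between people enters a correlation of levels in full and says nothing about whether the two measures move together after the intervention.

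The result would be presented under a change-over-time heading. A significant coefficient could be reported as evidence about change that it does not contain, and a real link between changes could be overlooked because stable levels dilute it. The shared-method problem that the Discussion concedes makes this worse: a stable response style feeds directly into correlations of levels but largely cancels in within-person differences.

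**Working it through.** **Sample size used.** Sample Size and Power Calculations states "The minimum sample for each group was identified as 64 participants to detect a power of 0.80 and an α of 0.05", with an allowance for 15% loss. 64 / (1 − 0.15) = 75.3, rounded up to 76 per group, and 2 × 76 = 152, which reproduces the plan's figure. The check uses 2 × 64 = 128 evaluable participants. The plan gives no figure for the correlation itself.

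**Assumed inputs (not in the document).** Between-person correlation ρ of the stable levels of quality of life and a secondary outcome: 0 to 0.7. Stability (ICC, the share of variance that is stable within a person): 0.5 to 0.8, with 0.7 for the simulations unless stated.

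**Model.** Score = stable person level + visit deviation, total variance 1. For unrelated changes, the visit deviations of the two measures are independent.

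**Reading 1: each person's mean over three visits.**

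r = ICC × ρ / (ICC + (1 − ICC)/3). At ICC 0.7 this is 0.7ρ / (0.7 + 0.1) = 0.875ρ. Results from 2,000 simulated trials with n = 128, tested at 0.05:

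| ρ | r of person means | significant | r of T0–T1 changes | significant |
|---|---|---|---|---|
| 0 | 0.00 | 5% | 0.00 | 4% |
| 0.1 | 0.09 | 18% | 0.00 | 5% |
| 0.2 | 0.17 | 50% | 0.00 | 5% |
| 0.3 | 0.26 | 85% | 0.00 | 5% |
| 0.5 | 0.44 | >99% | 0.00 | 6% |
| 0.7 | 0.61 | 100% | 0.00 | 5% |

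Over ICC 0.5 to 0.8 the formula gives r of 0.23–0.28 at ρ = 0.3, 0.38–0.46 at 0.5 and 0.53–0.65 at 0.7. The change-score correlation stays at zero because T1 − T0 removes the stable level.

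**Reading 2: scores at a single visit.** r = ICC × ρ. At ρ = 0.5 this is 0.25 (ICC 0.5) to 0.40 (ICC 0.8). It is smaller, but still purely cross-sectional.

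**Reading 3: aggregate means.** With one group there are 3 visit means; with two arms, 6. The simulation used 64 people per arm, ICC 0.7, ρ = 0.5 and unrelated individual changes. Both outcomes shifted together after baseline by 0.2 to 0.5 SD, with half that shift in the second arm when there are two. Median r was 0.92 to 0.99 with 3 points and 0.68 to 0.91 with 6. With no shift, 3-point correlations centre on zero but exceed 0.7 in absolute value in 53% of runs. Such a coefficient reflects parallel average trends or noise, not individual change.

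**Converse case.** Let visit deviations correlate at 0.5, so that changes also correlate at 0.5, and let stable levels be uncorrelated. The covariance of person means is 0.5 × 0.3/3 = 0.05 and their variance is 0.7 + 0.3/3 = 0.8, so r = 0.05/0.8 = 0.0625 (simulated 0.06). The change-score correlation recovers 0.50. The correlation of means all but misses a real link.

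**The case against.** The strongest defence is that this is one condensed sentence in a journal article. The purpose clause mentions change and the following paragraph names the three differences, so the authors may have meant mean changes. If so, the fault is one of wording. The unit of correlation and any adjustment could also properly sit in a fuller plan that is not shown. That much is fair, and omission of those details is not the complaint. But the sentence does state what is correlated, and it is not change; the differences are assigned only to the comparison between groups. A correction is needed on either reading.

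A reader might go further and infer that the analysis will show strong associations almost every time and so produce a false conclusion about mechanism. The document does not support that:

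- It gives no between-person correlation and no stability. Over the assumed range r runs from 0 to about 0.65, mostly weak to moderate, and is near zero for a secondary outcome unrelated to quality of life.
- The secondary outcomes are not all self-report scales. The MoCA is a neuropsychological test, so shared response style is not a general explanation.
- A significant correlation of levels is a correct finding about levels. It misleads only if read as change, and the hypotheses in the Introduction include no mediation or mechanism claim.
- The text does not say that the arms are pooled.

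The Discussion's caveat about false correlations counts for the authors in part: they know the hazard, although they describe it among items rather than between scales, and they do not connect it to this analysis.

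**Conclusion.** The point stands as a mismatch between a stated method and its stated purpose. None of the three readings of the means measures whether individual changes in quality of life and in a secondary outcome go together. The analysis can show a significant association when changes are unrelated, and it can miss an association when changes are related.

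The mismatch follows from the wording alone. Its size does not: it rests on the assumed two-component model, the assumed stability and between-person correlations, 128 evaluable participants and the choice of reading. The defensible claim is that significant associations can appear without related changes, and under the aggregate reading strong ones; not that they must. For DASS-21 and PSQI, where higher scores are worse, an association with quality of life would be expected to be negative.

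This is a minor point. The correlation is a supporting analysis, and neither the between-group comparison of the primary outcome nor the sample size depends on it.

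**What to change.** Choose one of two corrections in Statistical Analysis.

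1. **Keep the purpose and change the method.** State that each participant's change (T0 to T1, T1 to T2, T0 to T2) in the primary outcome scores is correlated with the same participant's change in each secondary outcome. Adjust for arm, by partial correlation or regression, and preferably for baseline values. Report as exploratory, with confidence intervals. Adjustment for arm matters here because Assessment and Outcomes has the intervention group answering on paper and the control group through SurveyMonkey: a mode effect or a treatment effect that moves several scales in one arm could by itself create a correlation if the arms are combined.
2. **Keep the method and change the purpose.** Describe the analysis as a cross-sectional association between levels, name the visit and the unit, and drop the reference to change over time.

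The first is better because it answers the question the authors pose. Even then the result is an association between changes and should not be reported as a mechanism. The cost is a sentence of text and a few lines of code; the data are already being collected.
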